### Blinding

This study used a single-blind design in which the outcome assessor is blinded to group allocation. Due to the nature of the intervention, complete blinding of caregivers and personnel administering the intervention was not feasible. However, efforts were made to minimize bias by standardizing procedures and ensuring that the assessor evaluating feeding cues was unaware of group assignments.

### Intervention

The intervention is initiated at the time of feeding preterm infants. For infants receiving CPAP, the olfactory stimulus is administered without interrupting respiratory support. A sterile gauze containing breast milk is positioned near the infant’s nose, outside the CPAP interface, allowing passive exposure to the odor without interfering with airflow or device function. This procedure was selected to maintain safety and permit intervention delivery during CPAP support. No modifications to the CPAP settings or interface were made during the intervention.

Prior to each intervention session, the infant’s respiratory condition is assessed to ensure adequate nasal patency. The intervention is performed only when there is no significant airway obstruction, excessive nasal secretions, or clinical instability that could interfere with olfactory perception. To minimize the influence of external odors, the intervention is administered immediately before scheduled feeding sessions in a consistent NICU environment. Wherever feasible, routine procedures involving strong odors, such as skin antisepsis or adhesive remover sprays, are completed before the intervention or delayed until after completion of odor exposure. Because complete elimination of environmental odors is not feasible in routine NICU practice, both the intervention and control groups receive identical routine clinical care under the same environmental conditions, thereby minimizing differential exposure to external odors.

One minute before feeding, breast milk odor was applied using sterile gauze placed near the infant’s nose and kept in place until feeding was completed. Feeding in this study is conducted according to standard NICU practice, primarily using intermittent bolus feeding via an orogastric tube. Breastfeeding attempts are introduced based on infant readiness as assessed by clinical staff. Each feeding session typically lasts approximately 15 to 30 minutes, depending on the infant’s tolerance and clinical condition.

The breast milk odor was administered 3 times daily for 3 consecutive days for a total of 9 feedings. An assessment of feeding cues was conducted using video recordings captured during the intervention. The videos were reviewed by a pediatric nursing specialist with at least 5 years of NICU clinical experience who was blinded to group allocation (intervention or control) using a feeding cue assessment instrument that had been tested for validity and reliability.

The breast milk used for olfactory stimulation was obtained from each infant’s own mother whenever available. Mothers were instructed to express breast milk using sterile techniques on the same day as the intervention. The expressed milk was labeled immediately after collection and stored at 2 °C to 4 °C for no longer than 24 hours before use. Prior to each intervention session, designated research personnel retrieved the breast milk from storage, allowed it to reach room temperature, and prepared the sterile gauze according to the standardized study protocol. In cases where maternal breast milk was unavailable or insufficient, donor breast milk was used with maternal consent.

The intervention is administered exclusively by trained research staff who are not involved in outcome assessment. The prepared breast milk was delivered to the intervention personnel immediately before each scheduled feeding session. All research staff received standardized training before study initiation to ensure consistent implementation of the intervention protocol across both study sites.

The 3-day intervention period was selected based on previous studies [9] and clinical evidence suggesting that short-term sensory stimulation in preterm infants can produce measurable effects on feeding behavior within 48 to 72 hours. Outcome measurements were conducted in parallel with the intervention sessions according to a predefined assessment schedule.

### Control Condition

The control group received an identical procedure using a clear, odorless, starch-based liquid designed to visually resemble breast milk while minimizing olfactory stimulation. The control fluid was prepared under sterile conditions and did not contain any volatile compounds associated with breast milk odor. The volume, timing, and duration of exposure were standardized and matched to those of the intervention group. The control condition was designed according to the principles of neutral olfactory control used in previous olfactory intervention studies to maintain procedural consistency while minimizing olfactory stimulation and sensory bias [21].

### Measures

The FCF-UF, originally developed by Yücel et al [9], is a structured instrument designed to assess feeding cues in preterm infants. The instrument evaluates behavioral state, rooting, sucking attempts, and physiological stability. The instrument consists of dichotomous items scored as either present (score 1) or absent (score 0). Individual item scores are summed to obtain a total feeding cue score, with higher total scores indicating greater feeding cues.

In this study, feeding cues were assessed using the Indonesian version of the FCF-UF, which was cross-culturally adapted and validated for use in the Indonesian NICU setting. During each feeding session, infants were video recorded, and the recordings were independently reviewed by a blinded pediatric nursing specialist with at least 5 years of NICU experience using the standardized FCF-UF scoring criteria. The Indonesian version demonstrated excellent internal consistency (Cronbach α=0.92), excellent test-retest reliability (intraclass correlation coefficient=0.99), and excellent construct validity based on confirmatory factor analysis (*χ*^2^_20_=17.4, root mean square error of approximation=0.000, comparative fit index=1.000, and Tucker-Lewis index=1.001) [22].

### Outcome Measures

The primary outcome of this study was feeding cues, as measured by the FCF-UF. Feeding cues were assessed 3 times daily during each feeding session over the 3-day intervention period (total of 9 assessments). The assessments were conducted using video recordings, which were evaluated by a blinded pediatric nursing specialist to ensure objectivity and reduce observer bias.

The secondary outcome was the time to first successful breastfeeding, defined as the duration (in minutes) from the onset of observable feeding cue behaviors until the infant achieved the first successful breastfeeding. Observable feeding cue behaviors included rooting, head turning toward the breast, mouth opening, and searching for the nipple following tactile stimulation. Successful breastfeeding is defined as effective latching onto the mother’s breast followed by coordinated sucking, swallowing, and breathing for a sustained period, as observed by trained clinical staff.

Although breastfeeding attempts may occur during routine clinical care during the 3-day intervention period, these routine attempts were not included in the assessment of the secondary outcome. To ensure a standardized observation period across all participants, the predefined secondary outcome (time to first successful breastfeeding) was prospectively measured beginning on day 4, after completion of the intervention. Observations were conducted daily for a maximum of 60 minutes per day and continued for up to 10 days or until successful breastfeeding was achieved.

This outcome was measured using a stopwatch starting from day 4 after completion of the intervention. The measurement of time to first successful breastfeeding therefore began after completion of the 3-day intervention period (day 4). Postnatal age and other relevant clinical variables were recorded and will be considered as potential confounders in the analysis.

All outcome data were recorded in structured electronic forms immediately after each assessment to ensure accuracy and completeness. The schedule of enrollment, intervention, and outcome assessments is presented in Table 1.

**Table 1. T1:** Schedule of enrollment, intervention, and outcome assessments.

Study phases	Day 0	Days 1‐3	Days 4‐10
Screening and eligibility	✓		
Informed consent	✓		
Randomization	✓		
Intervention (breast milk odor exposure)		✓^a^	
Feeding cue assessment (FCF-UF^b^)		✓^c^	
Time to first successful breastfeeding			✓^d^

a Intervention administered 3 times daily during days 1-3.

b FCF-UF: Feeding Cues Follow-Up Form.

c Feeding cues assessed 3 times daily during days 1-3 (9 assessments in total).

d Assessed daily from day 4 until successful breastfeeding or for a maximum of 10 days.

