To our knowledge, no previous multicenter randomized controlled trial has evaluated breast milk odor using a standardized intervention protocol together with repeated feeding cue assessments using a validated instrument, Feeding Cues Follow-Up Form (FCF-UF), in the Indonesian NICU setting. This study is expected to provide context-specific evidence that may inform neonatal nursing practice in similar resource-limited settings.

This study aims to evaluate the effects of breast milk odor stimulation on feeding cues and time to first successful breastfeeding in preterm infants admitted to the NICU. We hypothesize that preterm infants receiving breast milk odor exposure will demonstrate significantly higher feeding cue scores and achieve successful breastfeeding earlier than infants receiving the neutral odor control intervention. The findings may provide evidence to guide neonatal nursing practice, particularly in resource-limited settings.

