### Data Analysis

Data analysis will be conducted according to the intention-to-treat principle; therefore, all randomized participants will be included in the analysis according to their assigned groups, regardless of their adherence to the intervention. Outcomes will be analyzed using an independent *t* test for normally distributed data or the Mann-Whitney *U* test when normality assumptions are not met. If repeated measurements are available across multiple points, longitudinal analysis will be performed to more comprehensively assess response changes over time. For the secondary outcome of time to first successful breastfeeding, Kaplan-Meier survival analysis will be used, with between-group comparisons performed using the log-rank test. Infants who do not achieve successful breastfeeding within the 10-day observation period will be treated as censored observations. Intervention effects will be reported as the mean difference between groups, accompanied by effect sizes, using Cohen *d* to describe the magnitude of the intervention’s impact.

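### Time to first successful breastfeeding has two incompatible clocks (stopwatch minutes from cue onset, and days from day 4), so the log-rank test on the literal definition may not show whether infants breastfeed earlier

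*Protocol article*

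**What the plan says.** Outcome Measures defines the only secondary outcome as "defined as the duration (in minutes) from the onset of observable feeding cue behaviors until the infant achieved the first successful breastfeeding". The same section then says: "This outcome was measured using a stopwatch starting from day 4 after completion of the intervention". On the window it says: "Observations were conducted daily for a maximum of 60 minutes per day and continued for up to 10 days", or until success. Breastfeeding attempts during the three intervention days are set aside: "these routine attempts were not included in the assessment of the secondary outcome".

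Data Analysis prescribes Kaplan-Meier curves and a log-rank test, with this censoring rule: "Infants who do not achieve successful breastfeeding within the 10-day observation period will be treated as censored observations". It also commits to including every randomised infant.

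The hypothesis in the Introduction is that odor-exposed infants will "achieve successful breastfeeding earlier than infants receiving the neutral odor control intervention".

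**The concern.** A survival analysis needs one origin, one unit, and a censoring time on the same scale as the event times. Here the event is timed in minutes from a behaviour that starts at a different moment for each infant. The non-event is defined on a calendar of days. A second sentence moves the start to day 4.

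The article does not say:
- which cue episode starts the clock when success takes several days;
- whether the hours between sessions count;
- what value in minutes a censored infant carries;
- where time zero lies for an infant who shows no cues.

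The hypothesis concerns breastfeeding sooner. If the analysed variable does not order infants by how soon they breastfed, the test can miss a real gain, reverse it, or report one that is absent.

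**Working it through.** **Inputs from the article.** Sessions of at most 60 minutes a day for up to 10 days give at most 60 × 10 = 600 observed minutes, in separate blocks. The target is 48 infants per arm; 104 were enrolled, or 52 per arm if split evenly. No event rate, latency or power is stated for this outcome, so there is no figure to reproduce and the rates below are assumptions.

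**The possible readings.**
1. *Minutes within the successful session.* This is the natural reading of a stopwatch and a 60-minute limit. Success on the last day after 5 minutes counts as faster than success on day 4 after 20 minutes.
2. *Elapsed minutes from first cue.* An infant who cues on day 4 and succeeds two days later scores 2 × 24 × 60 = 2,880. An infant who succeeds at the same moment but first cued 15 minutes before scores 15. Earlier cueing lengthens the measured time, and cues are the primary outcome that odor is expected to raise. An infant who never cues has no start time, which conflicts with analysing all randomised infants.
3. *Cumulative observed minutes from day 4.* T = 60 × (k − 1) + m, where k is the observation day and m the minutes in the successful session; failures are censored at 600. This preserves the order of days, but it does not start at cue onset.

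**Why reading 1 loses the effect.** With daily success probability p, the share not succeeding in 10 days is (1 − p)^10. If latency is equal in both arms, the arms can differ on the minutes scale only through that share.
- 30% vs 50%: 0.7^10 = 2.8% against 0.5^10 = 0.1%, almost nothing to detect.
- 10% vs 20%: 0.9^10 = 34.9% against 0.8^10 = 10.7%, a gap of 24.2 points that the test can detect.

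**Simulation, first model.** There are 52 infants per arm, a geometric day of success, lognormal latency limited to 60 minutes, and a two-sided 5% log-rank test. Pairs are control vs odor. Ranges are over repeated runs.

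| Daily success | Median latency (min) | Rejects on days | Rejects on within-session minutes |
|---|---|---|---|
| 30% vs 50% | 15 vs 15 | 88–91% | 7–10% |
| 20% vs 35% | 15 vs 15 | 90–92% | 29–30% |
| 10% vs 20% | 15 vs 15 | 91–93% | 77–81% |
| 30% vs 50% | 15 vs 10 | as row 1 | 86% or more |
| 30% vs 50% | 15 vs 20 | as row 1 | under 0.1% for odor, about 30% for control |
| 30% vs 30% | 15 vs 10 | nominal | about 71% for odor |

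Latency does not enter the day scale. The last two rows correspond to a log-scale SD of latency of 0.6. In a check with 3,000 trials per setting, an SD of 0.5 gave 44% and 84%, and an SD of 0.8 gave 19% and 49%. The direction is stable but the size is not. Reading 3 kept about 87% to 91% power at equal latency.

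**Second model.** This uses 48 infants per arm, gamma latency (mean 15 minutes unless stated) and 1,000 trials per setting.
- 25% vs 45%, equal latency: 94% on days, 15% on minutes, 93% on the cumulative clock.
- 35% vs 60%, equal latency: 94% on days, 5% on minutes.
- 12% vs 22%, equal latency: 82% on days, 60% on minutes.
- 25% vs 45%, mean latency 12 vs 18 minutes: 93% on days; on minutes 0% for odor and 39% for control.
- 25% in both arms, mean latency 20 vs 12 minutes: 2.5% for odor on days, 79% on minutes.

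**The case against.** The best defence is the day-4 wording. The article says that measurement began on day 4 in order to standardise observation across infants, and this supports the cumulative reading, which keeps nearly all the power of the day scale. That is fair: the design is not necessarily unable to answer the question. But this reading contradicts the cue-onset clause, which is the formal definition, so it does not resolve the text.

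A second defence is that the low power rests on assuming equal latency. This also stands. If odor shortens latency as well as bringing success forward, power on minutes can be as high as on days. The article supports neither assumption with a figure. High power gained this way would still not separate faster latching from earlier breastfeeding.

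A third is that an article leaves detail to a fuller document. Here the article itself fixes the unit, origin, device, test and censoring rule, and it is these statements that conflict.

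A reader might also infer that randomisation no longer protects the comparison. The documents do not support that. If odor has no effect and every infant is analysed, the test keeps its level: null rejection in 1,500 simulated trials was 4.8% on minutes and 4.1% on days. The difficulty is what a difference means when odor does act, and what happens if infants without a cue are left out.

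**Conclusion.** The definition is wrong as written. Its two origins and scales are incompatible, and on the literal cue-onset clause the log-rank test may not show whether infants breastfeed earlier. Depending on success rates and latencies that the article does not give, the within-session scale can miss a gain in days (about 8% power against 88% to 91%), favour the wrong arm (about 30% of trials) or declare a benefit with no gain in days (about 71%).

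It would be too strong to say that the test cannot detect any benefit. Where many infants never succeed, it picks up the difference in that share, with about 80% power at 10% vs 20% daily success. That is evidence on the proportion succeeding rather than on earliness.

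The primary feeding-cue analysis is unaffected. The outcome nevertheless appears in the objective and hypothesis, and the abstract's conclusion about earlier initiation depends on it.

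**What to change.** For Kaplan-Meier and log-rank, define the outcome as the time in days from the start of observation on day 4 to the observation day of first successful breastfeeding, with this one origin for all infants. For infants followed from day 4, counting from day 0 adds a constant and leaves the log-rank result unchanged. Censor on the same scale at the end of the window or at last observation, and include infants who never cue. State the window length explicitly, because the column in Table 1 covers days 4 to 10 (seven days) while the text and footnote allow up to 10 days.

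State how successes on days 1 to 3, or outside the daily session, are handled. One option is a sensitivity analysis that counts any recorded success before day 4 as an event at the origin. Time from randomisation to the true first success should not be assumed available, since early attempts were not counted and observation covered at most an hour a day. Report minutes from cue to latch only as a descriptive latency among infants who succeed.

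The cost is a change of definition and a re-analysis. The article reports analysis complete in August 2026, so the change is post hoc: label it as a correction and report the published definition beside it. It relies on the session day of success having been recorded, which daily observation with immediate electronic entry makes likely but does not prove.

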### Data Management Plan

All data were recorded in electronic forms and stored on the principal investigator’s password-protected computer, accessible only to the principal investigator. Identity data were stored separately from the research data. Only the principal investigator had full access to the complete dataset.

### Safety Considerations

Breast milk odor stimulation is a safe and noninvasive intervention. Infants were monitored continuously during the intervention. If any deterioration occurred (eg, desaturation, bradycardia, or apnea), the intervention was discontinued and the infant was cared for according to NICU standards.

### Ethical Considerations

This study was approved by the Research Ethics Committee of the Faculty of Nursing, Universitas Indonesia (KET-007/UN2.F12.D1.2.1/PPM.00.02/2025), and by the Medical and Health Research Ethics Committee, Faculty of Medicine, Public Health, and Nursing, Universitas Gadjah Mada [name] Hospital (KE/FK/0979/EC/2025). The study was prospectively registered with the Indonesia Clinical Research Registry (INA-CRR) under registration number INA-5RCW7NLO on January 22, 2025, prior to participant recruitment [23].

Written informed consent was obtained from the parents of all participating infants prior to enrollment in the study. To ensure privacy and confidentiality, all collected data were deidentified and stored in secure, password-protected electronic systems accessible only to the principal investigator. Personal identifiers were removed from the dataset prior to analysis, and all procedures were conducted in accordance with applicable data protection standards. No financial or material compensation was provided to participants for participation in this study.

### Data Analysis

Data analysis will be conducted according to the intention-to-treat principle; therefore, all randomized participants will be included in the analysis according to their assigned groups, regardless of their adherence to the intervention. Outcomes will be analyzed using an independent *t* test for normally distributed data or the Mann-Whitney *U* test when normality assumptions are not met. If repeated measurements are available across multiple points, longitudinal analysis will be performed to more comprehensively assess response changes over time. For the secondary outcome of time to first successful breastfeeding, Kaplan-Meier survival analysis will be used, with between-group comparisons performed using the log-rank test. Infants who do not achieve successful breastfeeding within the 10-day observation period will be treated as censored observations. Intervention effects will be reported as the mean difference between groups, accompanied by effect sizes, using Cohen *d* to describe the magnitude of the intervention’s impact.

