### Sample Size Calculation

The sample size was calculated using G*Power version 3.1 based on an independent 2-group comparison (2-tailed independent-sample *t* test). Because previous studies investigating breast milk odor in preterm infants reported heterogeneous interventions, outcome measures, and effect estimates that were not directly comparable with the present study, a medium standardized effect size (Cohen *d*=0.50) was selected in accordance with Cohen’s recommendations for clinical research [20]. Assuming a 2-sided significance level of .05 and a statistical power of 80%, the minimum required sample size was 86 infants. To account for an anticipated 10% attrition rate, the final target sample size was increased to 96 infants, with 48 participants allocated to each group.

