### Comparison With Prior Work

Previous studies have consistently suggested that breast milk odor may improve feeding readiness and facilitate the transition to oral feeding in preterm infants. Recent systematic reviews and meta-analyses also reported beneficial effects on feeding outcomes, physiological stability, and selected clinical outcomes among preterm infants. However, these reviews also highlighted substantial heterogeneity in intervention protocols, outcome measures, participant characteristics, and methodological quality. Many included studies were conducted in single centers with relatively small sample sizes, limiting the strength and generalizability of the available evidence [4,6].

Among individual randomized trials, Yücel et al [9] demonstrated improvements in feeding cues and earlier transition to oral feeding following breast milk odor exposure, while Mohamed Soliman et al [13] reported enhanced feeding progression and behavioral responses. Despite these promising findings, differences in intervention delivery, assessment methods, and study design make direct comparisons difficult. These limitations underscore the need for standardized randomized controlled trials using validated outcome measures.

The present study was designed to address these gaps by using a multicenter randomized controlled design with concealed allocation, blinded outcome assessment, and a standardized breast milk odor protocol administered 3 times daily for 3 consecutive days. Unlike previous studies, feeding cues are assessed repeatedly using the validated FCF-UF, allowing comprehensive evaluation of behavioral changes over time. Conducting this study in 2 tertiary NICUs in Indonesia also provides context-specific evidence from a Southeast Asian setting where standardized developmental care interventions remain limited. Collectively, these methodological improvements are expected to strengthen the current evidence and support the integration of breast milk odor as a simple, low-cost intervention to promote feeding readiness in preterm infants.

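### Nine feeding-cue scores per infant are fixed by design, but the analysis rule does not tie them to one primary comparison

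*Protocol article*

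**What the plan says.** The Outcome Measures section fixes the structure of the primary outcome: "Feeding cues were assessed 3 times daily during each feeding session over the 3-day intervention period (total of 9 assessments". The Abstract, the Figure 1 legend (T1 to T9) and the notes to Table 1 agree. Under Comparison With Prior Work the repetition is presented as a strength: "feeding cues are assessed repeatedly using the validated FCF-UF, allowing comprehensive evaluation of behavioral changes over time".

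The Data Analysis section gives this rule: "Outcomes will be analyzed using an independent *t* test for normally distributed data or the Mann-Whitney *U* test when normality assumptions are not met". It continues: "If repeated measurements are available across multiple points, longitudinal analysis will be performed to more comprehensively assess response changes over time". On reporting it says: "Intervention effects will be reported as the mean difference between groups, accompanied by effect sizes", with Cohen d as the effect size. It promises an intention-to-treat analysis of every randomised infant.

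Under Sample Size Calculation the trial is sized on a two-tailed independent-sample t test, and "a medium standardized effect size (Cohen *d*=0.50) was selected". That section does not link d to a session, a mean or a time point, and it uses no within-infant correlation.

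The Abstract and Results report that statistical analysis was completed in August 2026. The Data Analysis section is still in the future tense.

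**The concern.** The rule does not fit the outcome. A two-sample test needs one number per infant, and the design produces nine. The article does not say whether that number is the nine-session mean, the last session, a daily mean or each session in turn. The analysis that would use all nine scores depends on a condition that the design has already met, and it is not ranked against the two-sample test. The choice between t and Mann-Whitney is itself left to the data. The mean difference to be reported has no stated summary or time point.

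Several different results could therefore be called primary. At stake are the 5% error rate of the primary claim, its power under some of the choices, and whether a reader can tell that the choice came before the results.

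**Working it through.** **Inputs from the article.** Nine scores per infant (Outcome Measures); two-sided .05, 80% power, d=0.50, 86 evaluable infants and a target of 96 (Sample Size Calculation); 1:1 allocation (Randomization and Allocation). This gives 86/2 = 43 evaluable and 96/2 = 48 targeted per arm.

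**Assumed.** The article gives no within-infant correlation ρ, so a range is shown. Scores are taken as equally correlated across sessions.

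**Step 1: the plan's own figure.** A two-sided two-sample t test with d=0.50, .05 and 80% power needs 63.8, so 64 per arm, or 128 in total. The stated 86 does not follow. The attrition step does: 86/0.9 = 95.6, rounded up to 96. The mismatch is a separate matter. It bears on this point only because 43 per arm gives 63% power, not 80%, for a t test on one value with d=0.50.

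**Step 2: if each of the nine sessions were tested at .05.** With independent sessions the chance of at least one P<.05 under no effect is 1 − 0.95⁹ = 0.370. With correlated sessions it was simulated (400,000 draws of nine equally correlated normal statistics, counting any |z|>1.96):

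| ρ | 0 | 0.5 | 0.8 | 0.9 |
|---|---|---|---|---|
| Chance of at least one false positive | 37% | 27% | 17% | 12% |

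Independence is implausible for one infant over three days, so the correlated columns are the more relevant ones.

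**Step 3: one session against the mean of nine.** Read d=0.50 as the effect at any single session, constant over sessions. The variance of the nine-session mean, relative to one session, is (1+8ρ)/9, so the effective effect size is 0.50/√[(1+8ρ)/9]. Power is from the noncentral t distribution.

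| Value tested | Relative variance | Effective d | Power, 43 per arm | Power, 48 per arm |
|---|---|---|---|---|
| One session | 1 | 0.500 | 63% | 68% |
| Mean of nine, ρ=0.5 | 0.556 | 0.671 | 87% | 90% |
| Mean of nine, ρ=0.7 | 0.733 | 0.584 | 76% | 81% |
| Mean of nine, ρ=0.9 | 0.911 | 0.524 | 67% | 72% |

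The 43-per-arm column is the main one because 86 is the article's evaluable number.

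**Step 4: the other reading of d.** If d=0.50 already describes the nine-session mean, averaging adds nothing to the power calculation, and power stays at 63% with 43 per arm.

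**The case against.** The strongest reply is that the longitudinal analysis is in fact committed: the text says it will be done when repeated measurements exist, and by design they exist. Its model and covariance are details that a full protocol or SAP commonly holds. This is fair, and the missing model specification is not the complaint. What stands is that the published rule puts a condition on something the design guarantees, names no value for the two-sample test, and does not say which analysis decides the trial.

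A reader might make four stronger inferences that the article does not support.

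- **That the plan wastes power.** The article does not say that one session will be tested. A t test on each infant's nine-session mean uses every score and, with complete data and a constant effect, loses essentially nothing against a mixed model. The power gap in step 3 belongs to one possible choice, depends on how d is read, and nearly vanishes at high correlation.
- **That nine tests at .05 are planned.** No section says so, and the reporting sentence speaks of the mean difference in the singular. The error rates in step 2 show what the wording leaves open, not what it prescribes.
- **That infants with missing sessions will be lost.** Incomplete sets are plausible, since the Safety Considerations section has the intervention discontinued on deterioration. But no complete-case rule is stated, and a mean of the available sessions keeps any infant with at least one score.
- **That the trial was really sized on repeated measures.** A between-groups repeated-measures calculation with f=0.25, three measurements and ρ=0.5 does return 86. The article mentions neither input and names a t test, so this cannot be concluded.

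**Conclusion.** The point holds: the stated rule does not fit a primary outcome of nine scores, and it leaves open several results that could each be called primary.

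The size depends on which choice was made. The false-positive risk would run from 12% to 37% in place of 5% if sessions were tested separately. The loss of power would run from about 4 percentage points (ρ=0.9) to about 24 (ρ=0.5) with 43 per arm if a single session were tested. It would be essentially nil if the nine-session mean were tested with complete data. These figures rest on assumed correlations, equal correlation between sessions and, for power, a constant per-session d of 0.50.

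What does not depend on any of these assumptions is the ambiguity. It matters more because the analysis is reported as finished and the article does not show when the primary result was chosen.

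**What to change.** Replace the t/Mann-Whitney rule for the primary outcome, and the conditional sentence, with one primary analysis:

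- A linear mixed model on all nine FCF-UF totals, with arm, session and site as fixed effects and infant as a random effect. Site belongs in the model because randomisation was done separately at each hospital. Gestational age is an optional covariate.
- The primary estimate is the arm difference averaged over the nine sessions, with a 95% confidence interval and one P value judged at .05.
- Per-session differences and the arm-by-session pattern are descriptive.
- The normality switch is dropped. Because the score is a bounded sum of 0/1 items, a site-stratified permutation test on each infant's mean score can serve as a robustness check.

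Date this choice, state whether it was made before or after results by arm were seen, and label it post hoc if after. Without that statement the new wording could pass off a late choice as prespecified.

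The cost is revised text and one model fit on data already collected. The downside is that an average over sessions is less sensitive than a last-session contrast if the effect appears only late.
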